## Abstract

**Introduction:**

The human papillomavirus (HPV) vaccine, administered in early adolescence, can substantially reduce cervical cancer incidence and mortality. However, lack of written parental consent is a key reason why some young women do not receive the vaccine. The national legal framework allows girls to be vaccinated without parental consent provided they are deemed Gillick competent, but there is some reticence about vaccinating without written parental consent. Self-consent procedures are being implemented in Bristol and South Gloucestershire. This study will examine the implementation, acceptability and impact of these new procedures.

**Methods and analysis:**

Statistical analyses of routine data from Public Health England and the Child Health Information System will test if there has been an increase in HPV vaccination uptake in two ways: (a) Is there an increase when comparing before and after the change in our intervention sites? and (b) Does the percentage change in our intervention sites differ from comparison sites (similar to our intervention sites in terms of initial HPV uptake, ethnicity and deprivation levels) in England where no such intervention took place and how? For the process evaluation, we will develop a logic model and use questionnaires, observations and audio-recorded interviews with young women, school nurses, school staff and parents to examine the context, implementation of self-consent and response to the new procedures.

**Ethics and dissemination:**

The University of Bristol Faculty of Health Sciences Research Ethics Committee and the National Health Service Health Research Authority provided approvals for the study. We will produce a report with recommendations about self-consent procedures in conjunction with key stakeholders. At least two papers will be written for publication in peer-reviewed journals and for conference presentations. A summary of results will be shared with participating immunisation nurses, school staff, young people and parents as requested.

**Trial registration number:**

ISRCTN49086105; Pre-results.

Strengths and limitations of this studyThe study addresses the lack of evidence about the impact and acceptability of self-consent procedures for the school-based human papillomavirus vaccination programme.The study will examine new self-consent procedures as they are implemented in routine practice.Although not a trial, the proposed statistical analyses of routine data will provide evidence of the impact of self-consent procedures on vaccine uptake.The process evaluation will identify barriers and enablers to self-consent for adolescent vaccinations.Findings from this mixed-methods study will inform recommendations for future practice, and may be relevant to other adolescent vaccination programmes.

## Introduction

### Inequalities in uptake of the human papillomavirus vaccine

High coverage of human papillomavirus (HPV) vaccination programmes in early adolescence can substantially reduce cervical cancer incidence and mortality.^1 2^ In the UK, the HPV immunisation programme, predominantly delivered through schools, is achieving overall high coverage, and estimates suggest it will save 400 women each year from developing cervical cancer.^3^ However, research suggests lower socioeconomic status (SES) and some ethnic groups are associated with lower uptake of HPV vaccination.^4 5^ The incidence of cervical cancer has been found to be higher in lower socioeconomic groups^5^ and these women are also less likely to access screening programmes than higher socioeconomic groups contributing to a higher mortality rate.^6^ Inability to access vaccination adds a further layer of health inequality. Furthermore, students in special schools or pupil referral units are much less likely to receive the vaccine^6^ and may require additional efforts by healthcare professionals to ensure they are vaccinated.^7^

Because of the preferred age for HPV vaccination (12/13 years), written parental consent tends to be sought. However, previous research examining facilitators and barriers to uptake of the HPV vaccine has shown that a lack of written parental consent is a key reason why some young women do not receive the vaccine.^8 9^ Furthermore, it is a barrier with potential to reinforce health inequalities since lack of written parental consent may also be related to lower SES and some ethnic groups.^8 9^

### Self-consent for HPV vaccination

In the UK, the legal framework allows girls to be vaccinated without parental consent provided they are deemed Gillick competent.^10^ However, WHO has acknowledged difficulties over consent for HPV vaccination because of the age of the target group, and suggests, at the very least, parents should be informed of the planned vaccination to provide an opportunity for the child to ‘opt out’ of the procedure.^11^ In England, National Health Service information about HPV vaccination states: “Although, as a parent, you’re asked to sign a consent form, it is up to your daughter whether she has the vaccine or not”^12^ and in Public Health England (PHE) guidance for healthcare professionals there is a lack of a clear directive about whether parental consent is necessary.^13^

This lack of clarity has implications for the vaccination process. Parental consent may be missing because of problems in returning paperwork, or because a parent is unwilling to allow their daughter to be vaccinated. In both cases, there may be young women who wish to receive the vaccination. However, some immunisation nurses and school staff appear reluctant to allow girls to make their own decisions about HPV vaccination because of concerns about generating antagonism between parents and the school or healthcare providers.^8^

The issue of vaccination without written parental consent needs clarification, and guidance about self-consent procedures is required. However, there is a paucity of peer-reviewed published research on the topic of self-consent for adolescent vaccinations. A study undertaken in the USA concluded that the inability of minors to consent for vaccines is a likely barrier to vaccination, and that interventions to increase adolescent vaccination should consider strategies that increase the ability of unaccompanied minors, particularly older minors, to receive vaccines within the context of legal, ethical and professional guidelines.^14^ Also in relation to the USA, Dempsey and Zimet suggest the debate over whether adolescents should be legally allowed to self-consent to vaccination is unresolved and could have a substantial impact on vaccination rates.^15^

In her doctoral thesis, Batista-Ferrer^16^ examined consent for the HPV vaccine in schools in Bristol, UK. Reasons recorded for why eligible girls did not receive the first dose of the HPV vaccine course revealed that lack of a signed parental consent form was the main reason (45.9%), while active refusal by parents occurred much less frequently (11.9%). Nevertheless, research indicates that immunisation nurses and school staff were unwilling to be held accountable if young women presented for HPV vaccination without parental consent.^7 16^

PHE data for 2014/2015 show some areas in the south-west of England with low uptake of HPV vaccination. For example, Bristol was ranked 112th of 119 English local authorities (LAs) (excluding London) and South Gloucestershire was 106th. Because of concerns about low uptake rates, staff at PHE (South West) developed a ‘South West Template Pathway on Self Consent for School Aged Immunisations’. The aim is to support provider organisations in implementing a self-consent process to support young people to easily access vaccines, support immunisers to feel confident about self-consent and to improve the uptake of immunisations.

The current research will focus on the practicality and acceptability of implementing the new self-consent procedures, and the potential impact on overall uptake and health inequalities. This will involve a systematic review of evidence relating to consent procedures for adolescent vaccinations, a process evaluation examining new self-consent procedures in two LAs in the south-west of England and an assessment of the impact of self-consent on overall uptake levels and in relation to SES, ethnicity and type of school.

## Methods and analysis

The full study comprises three key elements: a mixed-methods systematic review of the literature relating to adolescent self-consent for vaccines; process evaluation establishing a logic model for self-consent and examining the context, delivery and response to self-consent procedures for the HPV vaccination programme and statistical analyses of routinely collected data relating to HPV vaccination uptake. A protocol for the systematic review will be published elsewhere. Here, we focus on the statistical analyses of routine data and the process evaluation in Bristol and South Gloucestershire LAs.

### The new self-consent procedures

Information about the HPV vaccine, together with forms requesting parental consent, is distributed to young women at school to take home to their parents or carers. Previously, young women who had not returned a written parental consent form were not administered the vaccine at school. Under the new arrangements, information and parental consent forms are still provided by the school for the young women to take home to their parents or carers. Those who return a completed parental consent form agreeing for vaccination to take place are included in the school-based vaccination session, but in addition those who do not have a signed parental consent are also asked to attend the session where an attempt is made by the immunisation nurse to gain verbal parental consent over the telephone. Where this is achieved, the young women are offered the HPV vaccine. If the parent cannot be contacted, the immunisation nurse assesses the young woman’s competence using a checklist and records this in a form. If the young woman is deemed competent and wants to receive the vaccine, she is asked to sign the form. If she is not deemed competent, or there is reason to believe that it would cause problems at home if she received the vaccine without parental consent, the young woman is not given the vaccine. These young women are given information about alternative options to receive the vaccination, such as through a community-based clinic run by the immunisation team: a letter with information about dates is given to the young women at the school-based session.

### Statistical analysis of routine data

Statistical analyses will examine whether the intervention (implementation of self-consent) is associated with an increase uptake overall and whether it has the potential to reduce health inequalities.

Routine PHE surveillance reports HPV uptake by geographical area but does not provide data on uptake by other factors such as ethnic group, social position or type of school. We will examine HPV uptake by these factors by extracting information from the Child Health Information System (CHIS).^17^ Following on from our previous work,^5^ we will examine data in relation to the programme years 2014/2015 until the 2018/2019 to compare uptake since the two-dose HPV vaccination programme has been implemented. The data will be anonymised and transferred in an encrypted format from the host organisation to the University of Bristol where it will be securely stored according to the Data Protection (Amendment) Act 2003 and University of Bristol requirements.

The following variables will be available from PHE through extracting anonymous aggregate information from routine immunisation systems and CHIS: number of young people offered HPV vaccination; HPV uptake by source (school, primary care, other); consent (parental written, parental verbal, young women’s self-consent); ethnic group; index of multiple deprivation^18^; childhood vaccinations; school year; year of birth; school; local government area. These data can then be used in analyses of HPV uptake. Measures of effect will be expressed as ORs and risk differences (ie, percentage of HPV uptake before intervention minus percentage of HPV uptake during intervention).

We will test whether there has been an increase in the uptake of the HPV vaccination programme before and after the intervention in terms of risk difference (difference in two proportions and tests of null hypothesis that there has been no change in uptake). Initiation of HPV vaccination uptake is 84.5% in Bristol and 86.4% in South Gloucester. Each year, approximately 1900 and 1300 (overall 3200) are invited to participate.^19^ Therefore, there will be an 80% power to detect an increase in HPV vaccine uptake to the average in England (89.4%) and over 90% power to detect an increase to 95%. In addition, we will examine whether uptake among young people from less affluent areas, minority ethnic groups and in alternative educational settings has increased and whether there has been any unintended increase or reduction in health inequalities in relation to HPV uptake. We also will examine uptake for specific schools exposed to the intervention and assess whether there is an association between the intensity of implementation of self-consent procedures (as examined in the process evaluation) and HPV vaccine uptake.

The observational data will test whether there has been an increase in HPV vaccination uptake in two ways. First, is there an increase before and after the change in our intervention sites? Second, is there evidence that the percentage change in our intervention sites is different from other sites in England where no such intervention took place? In the second set of analyses, we will seek to select comparison sites that are similar to our intervention sites in terms of ethnic diversity and social position.

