### Process evaluation

The process evaluation will be conducted in line with the Medical Research Council guidance on process evaluation of complex interventions.^20^ An initial logic model will be developed, in consultation with health professionals, to show the hypothesised links between planned activities and inputs (self-consent procedures) and the sequence of short-term and medium-term outcomes (HPV vaccine implementation and uptake) that lead to desired longer-term outcomes (increased uptake, reduction in health inequalities). The initial logic model will be refined through experience and discussion as the study progresses, leading to an agreed logic model at the end of the study.

Context will be considered in relation to the socioecological model and will include examination of policy, organisational, interpersonal (family and peers) and intrapersonal factors. Questionnaires will be sent to a key contact in all secondary schools and relevant immunisation nurses in the two LAs. These will include questions about policies and procedures for HPV vaccination within schools. In addition, the researchers will compile fieldnotes when conducting observations and interviews in a sample of schools. Context will also be explored through interviews with a sample of immunisation nurses, school staff, young people and parents.

Similarly, the implementation and response to the new consent procedures will be examined through: questionnaires sent to a key contact in all secondary schools (including alternative educational settings) (n=58) and relevant immunisation nurses (n=5) in the two LAs; audio-recorded interviews (face to face or telephone) with relevant immunisation nurses, and more detailed qualitative research in eight schools (two mainstream and two alternative educational settings in each LA) purposively sampled in relation to type of school, HPV uptake, free school meal entitlement and percentage of students from minority ethnic groups. In these schools, more in-depth research will entail: audio-recorded focus groups or interviews (as preferred by participants) with approximately six young women; audio-recorded interviews with key school staff with responsibility for organising HPV vaccination sessions (one per school); observations of the process and setting for HPV vaccination and audio-recorded interviews or focus groups (as preferred by participants) with a purposive sample of approximately six parents per school.

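### The stated before/after test is a plain two-proportion comparison with no allowance for school, so its intervals are likely, though not certainly, too narrow

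*Protocol article*

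**What the plan says.** All references are to the protocol article.

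- **Test.** Statistical analysis of routine data defines the before/after question as a risk difference, a "difference in two proportions and tests of null hypothesis that there has been no change in uptake". The same section adds that "Measures of effect will be expressed as ORs and risk differences". Neither sentence names a variance method, a school term or a year term.
- **Numbers behind it.** The baseline is given as "Initiation of HPV vaccination uptake is 84.5% in Bristol and 86.4% in South Gloucester". The size of the yearly cohort follows: "Each year, approximately 1900 and 1300 (overall 3200) are invited to participate". From these the article derives its power statement, "80% power to detect an increase in HPV vaccine uptake to the average in England (89.4%) and over 90% power to detect an increase to" a second, higher target (95%).
- **Delivery.** Under The new self-consent procedures, girls with a completed parental form "are included in the school-based vaccination session". Girls without one are asked to attend the same session, where the nurse tries to telephone a parent and otherwise assesses competence.
- **Number of schools.** Process evaluation puts the questionnaire sample at "all secondary schools (including alternative educational settings) (n=58") in the two LAs.
- **Variation between schools.** The routine-data section also plans to look at uptake in individual schools and to relate it to how intensively each school implements self-consent.
- **Data.** School is among the variables listed as available.

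**The concern.** A plain two-proportion test takes its standard error from binomial variance over individual girls. Here the events that decide whether a girl is vaccinated are arranged by school: distributing forms, running the session, telephoning parents and assessing competence. Girls in one school in one year therefore share influences on uptake.

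A before/after contrast in the same schools removes the part of the school effect that stays constant. It does not remove the part that changes from one year to the next. The plan gives its own reason to expect such change: if implementation intensity differs between schools and affects uptake, the before/after change will differ between schools.

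What is at stake is mainly the false-positive rate and the width of the interval. Ordinary fluctuation in school uptake between years could be read as an effect of self-consent, in a study meant to support recommendations for practice.

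**Working it through.** **1. The plan's own power figure.** Pooled baseline = (1900 × 0.845 + 1300 × 0.864)/3200 = 2728.7/3200 = 0.8527. The rise to 0.894 is 0.0413. With girls independent and one year against one year, SE = √(0.8527 × 0.1473/3200 + 0.894 × 0.106/3200) = 0.0083. At a two-sided 5% level (assumed, since the article states neither level nor sidedness), power is 99.9%. By LA it is 99.4% for Bristol and 65.0% for South Gloucestershire. The stated 80% is not reproduced, so its basis is unknown. Nothing below relies on it.

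**2. Cluster size.** m = 3200/58 = 55.2 girls per school-year, taking schools as equal in size. Mainstream schools will be larger than alternative settings, so 55 probably understates the effect for most girls.

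**3. Variance ratio.** When different girls in the same schools are measured in each year, the true variance of the difference divided by the binomial variance is

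VR = 1 + (m − 1) × ICC − m × ICC × r,

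where ICC is the total intra-school correlation within a year and r is the correlation of a school's effect between years. The SE ratio is √VR. The real type I error of a nominal 5% test is 2 × [1 − Φ(1.96/√VR)]. The documents give neither ICC nor r; both are assumed ranges.

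Example, ICC 0.05 and r 0.8: VR = 1 + 54.2 × 0.05 − 55.2 × 0.05 × 0.8 = 1 + 2.71 − 2.21 = 1.50; SE ratio 1.23; type I error 11%.

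| Total ICC | r = 0: VR, SE ratio, type I | r = 0.8: VR, SE ratio, type I | r = 1: VR, SE ratio, type I |
|---|---|---|---|
| 0.01 | 1.54, 1.24, 11.4% | 1.10, 1.05, 6.2% | 0.99, 0.99, 4.9% |
| 0.02 | 2.08, 1.44, 17.4% | 1.20, 1.10, 7.4% | 0.98, 0.99, 4.8% |
| 0.05 | 3.71, 1.93, 30.9% | 1.50, 1.23, 11.0% | 0.95, 0.97, 4.4% |

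**4. Break-even.** VR = 1 when r = (m − 1)/m = 54.2/55.2 = 0.98, whatever the ICC. Below that the binomial SE is too small; above it, slightly too large.

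**5. Several years per period.** The article plans five programme years without giving the split. With a years before and b after, and the same r between any two years, both the true and the binomial variance scale with (1/a + 1/b). The ratios in the table therefore do not change.

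**6. LA-by-year fluctuation, a separate term.** With null binomial SE √(2 × 0.8527 × 0.1473/3200) = 0.0089, LA weights 1900/3200 = 0.594 and 1300/3200 = 0.406, and an assumed independent LA-by-year SD s, the added variance is 2s²(0.594² + 0.406²) = 1.035s². For s = 0.5 point the SE is 0.0102 and the type I error about 9%. For s = 1 point the SE is 0.0135 and the type I error about 20%. Modelling schools does not remove this term, and two LAs cannot estimate it.

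**The case against.** The strongest reply is that the article never says girls are treated as independent. Its wording names a contrast and a null hypothesis, the article condenses a fuller protocol, and a statistical analysis plan that is not shown may fix the variance method. It is true that independence is inferred from the named test. But a two-proportion test is a stated choice, and if followed as written it makes no use of school.

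Second, clustering alone does not make a before/after interval too narrow. This stands: with almost perfectly stable schools the plain interval is slightly too wide. A reader might infer from the uncorrelated case that the type I error simply is 11% to 31%. The documents do not support that, because they give no ICC and no between-year correlation.

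Third, a reader might infer that the study loses power or that its power statement ignored clustering. Neither can be shown. Binomial variance over 3200 girls per year gives 99.9%, not 80%, so how the 80% was obtained is unknown.

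Fourth, the planned comparison with other sites addresses change shared with those areas. That stands, but it does not deal with fluctuation specific to a school or to one of the two LAs.

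Finally, adjusting for differences in case mix between yearly cohorts might seem to belong here. It is a question of confounding, not of interval width, and the article promises only anonymised aggregate data, which may not support it.

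**Conclusion.** The concern holds in a limited form. The one before/after test the article states ignores school, although delivery is by school and the plan expects schools to differ in implementation. The intervals are therefore likely too narrow, and the main harm is false positives.

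The size cannot be fixed from the documents. It runs from no inflation (between-year correlation about 0.98 or more), through a type I error of about 6% to 11% (correlation 0.8), to 11% to 31% (uncorrelated). These figures rest on assumed total ICCs of 0.01 to 0.05 and 58 schools of equal size. That the intervals are certainly too narrow would be too strong a reading. No conclusion about power is drawn.

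**What to change.** - **Before/after analysis.** Replace the plain two-proportion test with a binomial or logistic model of uptake on period that includes school and school-by-year effects, or keep a simpler model with standard errors clustered on school. Report the marginal risk difference and OR from it, so the effect measures stay as planned. School is already a listed variable, and counts of girls offered and vaccinated by school and year are sufficient.
- **LA-by-year fluctuation.** State as a limitation of the before/after result that school-level methods do not capture it and that two LAs cannot estimate it.
- **Comparison-site analysis.** Take uncertainty from the variation in change between LAs, not from counts of girls; for example, rank the change in the two intervention LAs among the changes in the comparison LAs.

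The cost is wider intervals and slightly more programming.

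### The before/after test is stated as a crude difference of two proportions between successive school cohorts, so a change in cohort mix can bias it in either direction, although the main predictors of uptake are being extracted

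*Protocol article*

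**What the plan says.** All of the following is in the protocol article. Under 'Statistical analysis of routine data', the before/after question is to be answered by a risk difference, glossed as a "difference in two proportions and tests of null hypothesis that there has been no change in uptake". The effect measures are given in the same section: "Measures of effect will be expressed as ORs and risk differences (ie, percentage of HPV uptake before intervention minus percentage of HPV uptake during intervention"). No model, standardisation or adjustment is named for this contrast.

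On the time span, the section says "we will examine data in relation to the programme years 2014/2015 until the 2018/2019". The introduction gives the target age: "Because of the preferred age for HPV vaccination (12/13 years), written parental consent tends to be sought". Each programme year is therefore, in the main, a new cohort.

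On predictors, the introduction says that "research suggests lower socioeconomic status (SES) and some ethnic groups are associated with lower uptake of HPV vaccination". The variables to be extracted include "ethnic group; index of multiple deprivation^18^; childhood vaccinations; school year; year of birth; school; local government area". Their stated use is open: "These data can then be used in analyses of HPV uptake".

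Two further analyses bear on the point. One is by subgroup: "we will examine whether uptake among young people from less affluent areas, minority ethnic groups and in alternative educational settings has increased". The other compares the change in the intervention sites with the change in sites without the intervention, which the team will try to choose for similar ethnic diversity and social position (the abstract adds initial uptake).

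**The concern.** A difference of two proportions between periods equals the effect of the intervention only if the cohorts would otherwise have had the same uptake. If the share of girls from lower-uptake groups changes between periods, crude uptake changes too, with self-consent doing nothing. The article identifies such groups and plans to hold the data that would deal with a measured change of this kind, yet the stated test does not use them.

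The bias has no fixed sign. A falling share of lower-uptake groups would look like a benefit; a rising share would hide one. The before/after test is also presented as one of two tests in its own right, so its estimate is likely to be quoted alone.

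**Working it through.** **Inputs from the article.** Baseline uptake is 84.5% in Bristol and 86.4% in South Gloucestershire, with about 1900 and 1300 girls invited per year (3200 in all). The target is 89.4%.

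- Pooled baseline: (1900 × 84.5 + 1300 × 86.4) / 3200 = 85.27%.
- Planned rise: 89.4 − 85.27 = 4.13 points.

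**The plan's own figure.** The article gives 80% power for a rise to 89.4%. A plain two-proportion test with 3200 per period and two-sided 5% (assumed; no level is stated) gives 99.9%, so the 80% is not reproduced. That is a separate matter and nothing below depends on it.

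**Assumed inputs.** The article gives neither uptake by deprivation or ethnic group nor any change in mix. I assume a gap of 10 to 20 points between a lower-uptake group and the rest, and a change of 2 to 5 points in that group's share.

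**Bias.** With no intervention effect, change in crude uptake = gap × change in share.

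- Low: 0.10 × 0.02 = 0.2 points, or 0.2 / 4.13 = 5% of the planned rise.
- Middle: 0.15 × 0.05 = 0.75 points, or 18%.
- High: 0.20 × 0.05 = 1.0 point, or 24%.

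**Effect on the test.** With one year of 3200 in each period:

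- SE = √(2 × 0.8527 × 0.1473 / 3200) = 0.886 points.
- Smallest significant difference: 1.96 × 0.886 = 1.74 points.
- Rejection rate with no true effect = Φ(−1.96 + bias/SE) + Φ(−1.96 − bias/SE).

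| Bias (points) | Bias/SE | Two-sided rejection |
|---|---|---|
| 0.2 | 0.226 | 5.6% |
| 0.75 | 0.847 | 13.5% |
| 1.0 | 1.129 | 20.4% |

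**Direction.** At 0.75 points almost all of the 13.5% falls in one tail: Φ(−1.113) = 13.3% against Φ(−2.807) = 0.25%. It is a false claim of benefit only if the mix moves favourably. If it moves the other way, a true rise of 4.13 points would appear as 4.13 − 0.75 = 3.38.

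**More years.** Pooling years shrinks the SE but not the bias. If all five years were used (split assumed), a 0.75-point bias gives:

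- four years against one: SE = √(0.8527 × 0.1473 × (1/12800 + 1/3200)) = 0.700 points, rejection 18.8%;
- three years against two: SE = √(0.8527 × 0.1473 × (1/9600 + 1/6400)) = 0.572 points, rejection 25.9%.

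**Local authority mix.** The two authorities differ by 86.4 − 84.5 = 1.9 points. Even a 10-point shift between them moves pooled uptake by only 0.10 × 1.9 = 0.19 points. Pooling them adds almost nothing to the concern.

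**The case against.** The strongest reply is that a condensed article states an effect measure and a null hypothesis, and leaves the model to a fuller document. The sentence on using the extracted data in analyses of uptake does not rule out adjustment, and the ORs could come from a regression. That stands as far as it goes: a reader might infer that the plan excludes adjustment, or confines deprivation and ethnicity to subgroups and site selection, and the article says neither. But it does state a test for this question, and that test is crude. The point is to replace a stated method, not to ask for missing detail.

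A reader might also infer that any shift in mix will be taken for an intervention effect. The article does not support that. It asks about association, says the study is not a trial, adds the comparison-site analysis, and reports uptake by deprivation, ethnicity and setting, which could expose a shift. These are partial safeguards: sites with a similar profile do not correct a change confined to Bristol and South Gloucestershire, and the subgroup results are aimed at inequalities.

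Finally, the size is assumed throughout. One could assume a 20-point gap and a 10-point shift, which gives 2.0 points and 61.7% rejection, but nothing in the article makes so large a shift likely over these years. With a 15-point gap, mix alone would need a shift of 1.74 / 0.15 = 11.6 points to reach the significance threshold. At the low end the effect is trivial.

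**Conclusion.** The point holds in a limited form. The before/after test is written as an unadjusted comparison of different cohorts, with acknowledged predictors on the extraction list but not tied to it, so the estimate can be biased in either direction. Under the assumed gaps and shifts the bias is 0.2 to 1.0 points, well below the planned 4.1-point rise, so it would not by itself produce a rise of the planned size. It can still distort a smaller observed change and raise the error rate of the test, to about 13.5% in the middle case with 3200 per period. These figures illustrate sensitivity; they do not estimate the actual bias. The change is worth making because it is cheap and because the form of the data extract decides whether it remains possible.

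**What to change.** State that the main before/after risk difference and OR will be adjusted for, or standardised to, deprivation, ethnic group, childhood vaccination, school or school type, and local authority. A binomial regression on period and these covariates, reported as a marginal risk difference and an OR, would do this. Keep the crude difference as a description.

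Settle the data format before extraction. The article describes the extract as anonymous and aggregate; if it arrives as separate one-way totals, no later plan can adjust. Ask the Child Health Information System for anonymised record-level data, or for counts cross-tabulated by year and these factors.

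The cost is a sentence in the plan, modest analysis work and a somewhat larger data request. A fine cross-tabulation may create small cells, and girls with missing ethnicity or deprivation need a 'not recorded' category. School type is not itself on the variable list and would have to be derived from school. Adjustment removes only measured changes in mix. It does not remove a secular trend in uptake, for which the comparison-site analysis is still needed.
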